### General criteria for patient selection

All patients treated with RT or radiochemotherapy (RCHT) can be included in the trial if fulfilling the inclusion and exclusion criteria.

### Inclusion criteria

Patients meeting all of the following criteria will be considered for the trial:treatment with radiotherapyage ≥ 18 yearsability of subject to understand the nature and individual consequences of the clinical trialwritten informed consent (must be available before enrolment in the trial)

### Exclusion criteria

Patients presenting with any of the following criteria will not be included in the trial:any contraindication to acupunctureknown coagulopathy or anticoagulation therapy with bleeding time > 4 minutes, thrombocyte count < 50 000/μlmissing complianceskin disease in the region of the acupuncture pointsrefusal of the patient to take part in the studyparticipation in another clinical study or observation period of competing trials

### Statistical considerations

The study is powered to show that continuous acupuncture during RT can have a positive effect on QOL. ROSETTA is a prospective randomized trial comparing traditional (*verum*) acupuncture to control (*sham*) acupuncture. Randomization will be performed using automated information technology (IT)-based randomization, and patients will be allocated to groups by the Study Center within the Department of Radiation Oncology, Technische Universität München (TUM). Additionally, the study will evaluate whether acupuncture can reduce QOL-related side effects such as fatigue, headache, nausea etc.

All patient data on symptoms, side effects and QOL according to the QOL questionnaires will be documented in our dedicated study database. Evaluation of the primary endpoint (QOL) will be performed using the Wilcoxon test (*U* test) and the evaluation tool provided by the EORTC. The secondary endpoints (fatigue, headache, nausea etc.) will be evaluated using comparable statistical calculations. The interpretation of the data will be purely descriptive.

The sample size calculation is based on the Wilcoxon test and the primary endpoint. A sample size of 37 patients per group (i.e. 74 patients in total) is associated with power of 80% to detect a difference between the two groups (with two-sided α = 5%) using the Wilcoxon test, with a probability of 69% that an increase in QOL can be achieved when comparing the two groups 8 (d.h. P(x < y).

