### Study design

The ROSETTA trial will evaluate the effect of acupuncture as a complementary treatment parallel to RT. Acupuncture is an established and accepted treatment method, which is indicated especially for pain reduction. The plan for study is to recruit 74 patients. The total study duration is planned to be 24 months.

After inclusion into the study and baseline examination, the patient is randomized into the treatment arm. Randomization is performed under the auspices of the biometrician. The randomization process will be performed with the professional web-based patient randomization service, e.g. at www.randomizer.at. The investigator or an authorized member of the study team will perform data documentation and evaluation.

Depending on the treatment arm either *verum* or *sham* acupuncture will be applied [23, 24, 26, 28, 30, 31]. Acupuncture will be performed after treatment bi-weekly during the first week of RT, thereafter weekly until the end of RT. Treatment time in both arms is identical and lies between 20 and 30 minutes. Every patient will be treated according to the treatment arm. Standardized acupuncture needles (sterile needles, e.g. 0.24 × 40 mm) will be used for both treatment types. *Verum* acupuncture is based on foraminology, the ancient Chinese knowledge of acupuncture points [32]. Control acupuncture is performed on unspecific points with no specific effect according to foraminology.

Patients will receive standardized questionnaires (European Organization for Research and Treatment of Cancer (EORTC) QLQ C-30) before their first, after their fourth and after their last acupuncture treatment. Patients will be questioned by the investigator about their feelings and symptoms and detailed information about their illness. The answers will be documented according to the standardized scoring system (Common Toxicity Criteria for Adverse Events (CTCAE)). The schedule of enrollment, interventions and assessments in the ROSETTA trial is depicted in Fig. 1.

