### Baseline examination

After informed consent and inclusion into the study protocol, a baseline examination will be performed. This examination is to be performed within 2 days before initiation of study treatment and includes:complete medical history including concomitant treatmentsclinical examination according to the regulation of TCMascertainment of QOLquestionnaire on fatiguedocumentation of any symptoms and sequelae prior to radiotherapy

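### The primary quality-of-life comparison is an unadjusted Wilcoxon test although QLQ-C30 is collected at baseline: valid, but it gives up power that adjustment would supply at almost no cost

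*Protocol article*

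**What the plan says.** Statistical considerations fixes the primary analysis: "Evaluation of the primary endpoint (QOL) will be performed using the Wilcoxon test". No covariate or stratum is attached to the test. The sample size is built on it: "A sample size of 37 patients per group (i.e. 74 patients in total) is associated with power of 80% to detect a difference", "with two-sided α = 5%) using the Wilcoxon test", the effect being expressed as "with a probability of 69% that an increase in QOL can be achieved when comparing the two groups".

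Study design has patients complete the QLQ-C30 "before their first, after their fourth and after their last acupuncture treatment". Baseline examination includes quality of life and says: "This examination is to be performed within 2 days before initiation of study treatment". A pre-treatment score is therefore planned for every patient.

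Follow up places the assessment of the primary endpoints at the final visit, 6 weeks after treatment. Neither Endpoints of the study, which speaks of improvement, nor the power sentence, which speaks of an increase, says whether the ranked quantity is the score at that visit or its change from baseline. Entry is broad: "All patients treated with RT or radiochemotherapy (RCHT) can be included in the trial".

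**The concern.** A questionnaire score at follow-up usually correlates with the same patient's score at entry. A two-sample rank test on follow-up scores leaves that variation in the noise. With 37 per arm, a chance difference in baseline quality of life also goes uncorrected in the estimate. Ranking change scores uses the baseline, but with a fixed slope of one rather than the slope that the data support.

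At stake is the power of a small trial planned at 80%, with little to spare for dropout, and the precision of its effect estimate. The choice of test is not left open for a later analysis plan: the article names it and sizes the trial on it.

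**Working it through.** **Inputs from Statistical considerations:** two-sided α = 5%, power 80%, 37 per arm, P(x<y) = 0.69.

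**Assumptions:** baseline-outcome correlation r = 0.3, 0.5 or 0.7 (not in the document), normal scores with equal variances, and no missing data.

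**1. The plan's own figure.** Noether's formula with equal allocation:

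N = (z₀.₉₇₅ + z₀.₈₀)² / [12 × 0.25 × (0.69 − 0.5)²] = 7.849 / 0.1083 = 72.47, so 37 per arm.

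Power at N = 74 is Φ(√(3 × 74) × 0.19 − 1.960) = Φ(0.871) = 80.8%. The stated sample size is right for the stated test.

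**2. Standardised effect.** For normal scores, d = √2 × Φ⁻¹(0.69) = 1.414 × 0.496 = 0.701.

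**3. Reading A: the 0.69 refers to final scores.** Baseline adjustment multiplies the residual variance by 1 − r², so the effect becomes d/√(1 − r²). Approximate ANCOVA power is Φ(effect × √(37/2) − 1.960), with √(37/2) = 4.301. The Wilcoxon-equivalent size per arm is 72.47 × (1 − r²)/2, rounded up.

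| r | 1 − r² | Adjusted effect | ANCOVA power (formula) | Equivalent n per arm |
|---|---|---|---|---|
| 0.3 | 0.91 | 0.735 | 88.5% | 33 |
| 0.5 | 0.75 | 0.810 | 93.6% | 28 |
| 0.7 | 0.51 | 0.982 | 98.8% | 19 |

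Simulated power at 37 per arm, with repeat runs agreeing to within one or two points:

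| r | Wilcoxon, final score | ANCOVA | Wilcoxon on baseline residuals |
|---|---|---|---|
| 0 | 83% | 84% | 83% |
| 0.3 | 82% | 87% | 85% |
| 0.5 | 82% | 92% | 91% |
| 0.7 | 82% | 98% | 98% |

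The formula runs slightly high because it ignores the t distribution.

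**4. Reading B: the 0.69 refers to change scores.** The standard deviation of change is √(2(1 − r)) in units of the score's standard deviation, so the planned shift is 0.701 × √(2(1 − r)). Dividing by √(1 − r²) gives an ANCOVA effect of 0.701 × √(2/(1 + r)).

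| r | ANCOVA effect | ANCOVA power (formula) | ANCOVA power (simulated) | Wilcoxon on change (simulated) |
|---|---|---|---|---|
| 0.3 | 0.870 | 96.3% | 96% | about 83% |
| 0.5 | 0.810 | 93.6% | 94% | about 83% |
| 0.7 | 0.761 | 90.5% | 89% | about 83% |

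Here the gain shrinks as r rises, because the change score then captures more of what adjustment offers. It does not vanish in this range.

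**5. Robustness and validity.** Under reading A, with scores made discrete and bounded from 0 to 100, ANCOVA still reached 86%, 90% and 98%. In null simulations the type I error was 4.7% for the Wilcoxon test on final scores, 5.0% for ANCOVA and 4.7% for the residual rank test.

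**The case against.** The strongest reply is that nothing is wrong. Under randomisation the Wilcoxon test controls its error rate, it agrees with the sample size calculation, and a rank test is a sensible choice for a bounded, discrete questionnaire score. This is also a phase II trial whose interpretation is declared purely descriptive. The validity part stands in full. It does not defend leaving the baseline out: the residual rank test stays in the rank framework, the gain persists on a bounded discrete score, and a descriptive estimate is less precise without adjustment too.

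A second reply is that the size of the gain rests on r, which the document does not give. That also stands, so the figures are a range. The direction does not depend on a favourable r, since at r = 0 adjustment loses nothing material.

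Three stronger readings are not supported:

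- A reader might infer that ranking change scores would leave the trial below 70% power at r = 0.3. That figure arises only if the 0.69 is set on the final-score scale and the test is then run on change. If change is what is ranked, the natural reading is that the 0.69 describes change, and power is about 83% at each r.
- A reader might infer that the mix of tumour sites and of RT with RCHT causes a further, measurable loss. The document gives neither the shares nor their relation to quality of life, so no size can be attached.
- A reader might infer that randomisation is unstratified. The article is silent on this, and a condensed article commonly leaves such detail to the full protocol.

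**Conclusion.** The point holds as a loss of efficiency, not of validity, and it is not an error in the sample size. Under reading A, baseline adjustment adds about 5, 10 and 16 percentage points of power with ANCOVA (87, 92 and 98 against 82) for assumed r of 0.3, 0.5 and 0.7. Under reading B it adds about 13, 11 and 6 points (96, 94 and 89 against 83). If change is ranked, the baseline is already partly used, so the loss is incomplete use rather than outright discarding.

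The direction is firm. The size rests on the assumed r, near-normal scores and complete data. Only the baseline quality-of-life score supports a quantified claim.

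**What to change.** In Statistical considerations, make the primary analysis a baseline-adjusted comparison of the QLQ-C30 score at the time point that Follow up sets for the primary endpoints. Use either:

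- ANCOVA with the baseline score as covariate; or
- to stay with ranks, the Wilcoxon test on residuals from the regression of the outcome on baseline.

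RT versus RCHT may be added as a factor, with a gain that cannot be quantified from the document. Keep the plain Wilcoxon test and P(x<y) as a sensitivity analysis, which also preserves the link to the sample size calculation.

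The cost is wording and slightly more analysis work, with no new data, visits or patients. With ANCOVA the headline effect becomes an adjusted mean difference, so P(x<y) should be reported beside it. Recruitment was still under way when the article was submitted; the change should be recorded before anyone sees outcome data by arm.

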### Follow up

The final study visit will be 6 weeks after treatment to assess the primary endpoints. After the first 6 weeks, patients will be included into a regular follow-up schedule according to their primary disease and follow-up requirements.

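### The 74 patients to be recruited are the uninflated calculated number, so the stated 80% power holds only if almost every randomised patient provides a primary QOL score

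*Protocol article*

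**What the plan says.** The Statistical considerations section of the protocol article bases the sample size on the primary endpoint, QOL: "The sample size calculation is based on the Wilcoxon test and the primary endpoint". It then states: "A sample size of 37 patients per group (i.e. 74 patients in total) is associated with power of 80% to detect a difference". The error rate is fixed "with two-sided α = 5%) using the Wilcoxon test", and the effect is expressed "with a probability of 69% that an increase in QOL can be achieved when comparing the two groups", that is, as P(x<y) = 0.69.

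The Study design section says: "The plan for study is to recruit 74 patients". The Abstract assigns 37 patients to each arm. The article mentions no loss rate, no inflation of the calculated number and no replacement of patients.

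On when the outcome is measured, the Study design section schedules the QLQ-C30 before the first, after the fourth and after the last acupuncture session. The Follow up section says: "The final study visit will be 6 weeks after treatment to assess the primary endpoints".

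**The concern.** A sample size formula gives the number of patients whose outcome enters the test. Here that number and the recruitment target are the same, so the stated power presumes nearly complete primary data.

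Some loss is foreseeable:
- The trial is open to any adult receiving radiotherapy or radiochemotherapy, with no entry limit on prognosis or performance status.
- The outcome is a questionnaire that the patient has to fill in.
- On either schedule, the last score is due only after repeated needling sessions over a course of radiotherapy.
- The compliance criterion acts at entry and cannot prevent later illness, withdrawal or blank forms.

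If scores are lost, a non-significant comparison would be read against a power that the trial did not have.

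**Working it through.** **Inputs.** From Statistical considerations: two-sided α = 5%, power 80%, P(x<y) = 0.69, Wilcoxon rank-sum test, 37 per group. From Study design: 74 recruited. From the Abstract: equal arms. The loss rate is not given, so 5–20% is assumed, with equal loss in both arms and unrelated to outcome, and with patients lacking a score left out of the test.

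**Reproducing the plan's figure.** Noether's formula with equal allocation is

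N = (z₀.₉₇₅ + z₀.₈₀)² / [12 × 0.25 × (P − 0.5)²] = (1.960 + 0.8416)² / (3 × 0.19²) = 7.849 / 0.1083 = 72.47.

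This is 36.24 per arm, rounded up to 37 per arm and 74 in total. The plan's figure is reproduced, and it contains no allowance for loss. A one-sided test would give 57.1, hence 58 in total, which does not match.

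**Power with fewer scores.** By the same formula, power = Φ(√(3N) × 0.19 − 1.960).
- N = 74: √222 × 0.19 = 2.831, and Φ(0.871) = 80.8%.
- N = 73: 80.3%.
- N = 72: 79.7%.

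The slack left by rounding is therefore about one patient.

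**Detectable effect.** The effect detectable with 80% power is P = 0.5 + 2.8016 / √(3N).

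**Cross-check.** A Mann-Whitney test was simulated under a normal shift of √2 × Φ⁻¹(0.69) = 0.70 SD, with 20,000 runs per setting. The Monte Carlo standard error is about √(0.8 × 0.2 / 20,000) = 0.3 percentage points.

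| Assumed loss | Patients with a score | Power, formula | Power, simulation | P detectable at 80% (formula) |
|---|---|---|---|---|
| 0% | 74 | 80.8% | 82.8% | 0.688 |
| about 5% | 70 | 78.6% | 80.3% | 0.693 |
| about 10% | 67 | 76.8% | 79.0% | 0.698 |
| about 15% | 63 | 74.3% | 75.5% | 0.704 |
| about 20% | 59 | 71.5% | 73.3% | 0.711 |

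The rows use whole patients. With exactly 5% and 20% lost (70.3 and 59.2 patients), the formula gives 78.8% and 71.6%. The simulated values are somewhat higher because the formula uses the variance under the null hypothesis.

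**The case against.** The sample size sentence is true as written: 37 per group with a score does give 80% power. A reader might infer that the number is miscalculated. It is not, since the formula returns it exactly.

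A reader might also infer that all 74 scores are needed, or that any realistic loss forfeits the 80%. Neither follows. By the formula 73 scores give 80.3%. Under the normal-shift model, 35 per arm still give about 80%, and 67 patients miss by only about one point. Every loss rate used here is an assumption, and so is the normal shift.

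Other points on that side:
- **Descriptive interpretation.** Statistical considerations says that the data will be interpreted purely descriptively. This lowers the stakes. It does not withdraw the power claim, because the same section says the study is powered for QOL and gives an α and a power.
- **Timing.** If the primary score is the one taken after the last acupuncture, while patients still attend for radiotherapy, losses may be smaller than at a visit six weeks later. The article does not settle which applies. This affects the likely size of the loss, not the absence of a margin.
- **Condensed article.** Handling of missing scores and replacement of patients may be set out in a full protocol or analysis plan that is not shown, so their absence is not held against the article. What stands is what the article itself fixes: a recruitment target equal to the calculated number, with 80% power attached to it.

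**Conclusion.** The point holds in a limited form. The calculation is correct for patients with a primary score, but recruitment is set at that same number, so the 80% is close to a best case.

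The shortfall is negligible at 5% loss: 1 to 2 points by the formula, none by simulation. It is clear from about 10%, where power is 77–79%. At 20% it reaches about 7 to 9 points, with power of 72–73%. In terms of effect, the P(x<y) detectable with 80% power rises from 0.69 to about 0.70–0.71.

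These sizes rest on the assumed loss rates, on equal loss in both arms unrelated to outcome, and on a test that uses only observed scores. The absence of a margin rests on the article's own figures.

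**What to change.** Keep 74 patients and restate the power in Statistical considerations, for example: *Thirty-seven per group is the number required with a primary QOL score. With 74 patients randomised and an assumed 10–20% without such a score, power for P(x<y) = 0.69 is about 72–79%; 80% power is reached for P(x<y) of about 0.70–0.71.*

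The range runs from the formula at 20% loss to the simulation at 10% loss. By one method alone it is 72–77% (formula) or 73–79% (simulation). The sponsor should substitute its own expected loss rate if it has one.

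The cost is a slightly less favourable stated power. No further patients are needed and the Wilcoxon analysis is unchanged. For scale, keeping 74 scores by recruiting more would take 74/0.9 = 82.2, hence 84 with equal arms, at 10% loss, and 74/0.8 = 92.5, hence 94, at 20%. Replacing the primary analysis with a model of all post-baseline scores is not part of this fix: it would be a larger change, and the Wilcoxon power figures above would not apply to it.

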### Data management

In the ROSETTA trial the EORTC QLQ-C30 will be used to document the QOL of patients during treatment. Data on side effects and symptoms during RT will be documented on dedicated case report forms (CRFs) designed for the trial and documented in the institutional database. All interventions and every other medical treatment will be recorded. The data will be collected in accordance with all Data Protection Regulations in the MiRO Database of the Department of Radiation Oncology, TUM.

## Discussion

Several studies have shown that traditional acupuncture can alleviate clinical symptoms: In Germany, especially for back pain, a multicenter study group has shown solid data in this regard and provided a strong basis for the use of acupuncture in this regard [16–21].

In oncology, a main focus of acupuncture treatment centers is to reduce RT-related side effects of either chemotherapy or RT. Meng et al. showed that acupuncture can prevent RT-related xerostomia in patients with nasopharyngeal cancer [7, 8]; Lu et al. focused on dysphagia in patients treated with RCHT for tumors of the head and neck, and observed a substantial effect of acupuncture [33]. A comprehensive review on acupuncture in cancer treatment illustrated that there have been 41 randomized controlled trials involving eight different symptoms, such as pain, nausea, hot flashes, fatigue, xerostomia, prolonged postoperative ileus, anxiety/mood disorders and sleep disturbance [34]. Cochrane criteria were used to classify the studies for risk of bias. Only a few studies were identified to be free of risk of bias, or to have a low risk of bias. Thus, more trials focusing on clear questions and applying valid control arms are needed to further clarify the role of acupuncture in oncology care.

To address these questions, the ROSETTA trial was set up as a prospective randomized controlled trial. In the control arm, sham-acupuncture points not associated with any function in the doctrine of TCM are applied (*sham* acupuncture). This concept has been applied in different trials, in patients with and without cancer [3, 7, 8, 23, 24, 33, 35, 36]. Compared to a pure non-treatment controlled trial, the bias of no treatment is not included in this trial concept. In the experimental arm, valid acupuncture points are used, which are known to reduce the associated side effects (*verum* acupuncture). Therefore, the ROSETTA trial will help to clarify the assumed benefit of acupuncture in terms of fatigue and QOL in the oncology setting in patients treated with RT Additional file 1.

### Status of the trial

Recruitment into the ROSETTA trial is ongoing at the time of submission.

## Abbreviations

CAM: Complementary and alternative medicine
EORTC: European Organization for Research and Treatment of Cancer
QOL: Quality of life
RCHT: Radiochemotherapy
RT: Radiotherapy, radiation therapy
TCM: Traditional Chinese medicine, TUM, Technische Universität München
